**Figure 2 F2:**
[figure not shown]
Intervention flow chart.

### Sample size considerations

As there has been a lack of published studies in this field power calculations have been based upon related review studies in the field of exercise and mental health. Power calculations are based upon physical self-perceptions as the primary outcome measure; (predicted effect size = 0.6, providing 80% power, p < 0.05) indicating 30 participants would be needed for each group (n = 90). A 25% dropout rate has been assumed at eight weeks from baseline indicating that 122 participants might need to be recruited.

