**Method/design:**

SHOT is a randomised controlled trial where obese young people are randomised to receive; (1) exercise therapy, (2) attention-control intervention (involving body-conditioning exercises and games that do not involve aerobic activity), or (3) usual care. The exercise therapy and attention-control sessions will take place three times per week for eight weeks and a six-week home programme will follow this. Ninety adolescents aged between 11–16 years referred from a children's hospital for evaluation of obesity or via community advertisements will need to complete the study. Participants will be recruited according to the following criteria: (1) clinically obese and aged 11–16 years (Body Mass Index Centile > 98^th ^UK standard) (2) no medical condition that would restrict ability to be active three times per week for eight weeks and (3) not diagnosed with insulin dependent diabetes or receiving oral steroids. Assessments of outcomes will take place at baseline, as well as four (intervention midpoint) and eight weeks (end of intervention) from baseline. Participants will be reassessed on outcome measures five and seven months from baseline. The primary endpoint is physical self-perceptions. Secondary outcomes include physical activity, self-perceptions, depression, affect, aerobic fitness and BMI.

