### Study design and setting

SHOT is a pragmatic randomised controlled trial where obese young people aged 11–16 years are randomised to receive exercise therapy, usual care or an attention-control intervention. The study sample will consist of adolescents who have been referred to a children's hospital in the United Kingdom (UK) for evaluation of obesity or via community and media advertisements publicising the study. Participants recruited by community adverts will have their medical eligibility to enter the trial confirmed by one of the study paediatricians (third and fourth authors). In order to facilitate recruitment and retention a £25 sport store voucher will be given to participants at the end of the intervention phase and a contribution of £2.50 towards travel expenses will be made per visit.

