### Statistical analysis

Differences in primary and secondary outcomes between control and intervention groups will be compared using intention to treat analysis. Imputation methods will be used to assess data losses through level drop out and loss to follow up. All results will be reported as means and 95% confidence intervals.

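### The stated 80% power does not follow from the printed inputs: an effect size of 0.6 with 30 completers per group gives about 63% in a two-sided pairwise comparison

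*Protocol article*

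**What the plan says.** The section Sample size considerations names the outcome: "Power calculations are based upon physical self-perceptions as the primary outcome measure". It takes its effect size from reviews of exercise and mental health, and gives the inputs and the result together: "predicted effect size = 0.6, providing 80% power, p < 0.05) indicating 30 participants would be needed for each group (n = 90".

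The 90 are completers. The Abstract (Method/design) says that ninety adolescents "will need to complete the study", and dropout of 25% is added afterwards to reach 122 recruited. The Abstract repeats the number but gives no power, effect size or significance level, so it confirms what 90 means and is not a second instance of the problem.

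There are three arms, with participants "randomised to receive exercise therapy, usual care or an attention-control intervention". The Statistical analysis section plans an intention-to-treat comparison of control and intervention groups and adds: "All results will be reported as means and 95% confidence intervals". Neither section names the test, its sidedness, the definition of the effect size, a baseline covariate or an assumed correlation.

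**The concern.** The article prints a complete calculation, with effect size, power, significance level and resulting group size, so a reader can check it. On the usual reading of those inputs the group size comes out half as large again as the one printed. This is the only justification of the sample size, and it concerns the primary outcome. If the usual reading is the intended one, the chance of missing a true 0.6 SD effect in a pairwise comparison is about 37%, not 20%.

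**Working it through.** **Inputs.** From Sample size considerations: effect size 0.6, power 80%, p < 0.05, 30 completers per group, 90 in all. Two readings are assumptions:
- 0.6 is a standardised mean difference, d (SD = 1), which is the usual meaning of an effect size taken from reviews.
- The test is two-sided, which fits the planned 95% confidence intervals.

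**Step 1: try to reproduce 30 per group.** Normal approximation for two equal groups:

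n per group = 2 × (1.960 + 0.842)² / 0.6² = 2 × 7.85 / 0.36 = 43.6, so 44.

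The exact noncentral-t calculation gives 44.6, so 45 per group (power at 45: 80.4%), or 3 × 45 = 135 completers. The printed 30 is not reproduced.

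**Step 2: power at 30 per group.** The noncentrality is 0.6 / √(2/30) = 2.32. The normal approximation gives Φ(2.324 − 1.960) = 64.2%. The t-test gives 62.8%, so the type II error is 100 − 62.8 = 37.2%. Taking the error variance from all three groups (87 degrees of freedom) gives 63.2%.

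**Step 3: detectable difference.** With 30 per group, a two-sided 5% level and 80% power, d = 0.736, about 0.74 SD.

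**Step 4: other readings of the same inputs** (5% level, 90 completers):

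| Reading | Power | Size for 80% |
|---|---|---|
| Two groups, two-sided | 62.8% | 45 per group |
| Two groups, one-sided | 74.3% | 36 per group |
| Exercise (30) v pooled controls (60), two-sided | 75.6% | 34 in the exercise arm |
| Exercise (30) v pooled controls (60), one-sided | 84.6% | 27 in the exercise arm |
| Three-group F-test, largest difference 0.6 SD, third mean midway (f = 0.6 × √(1/6) = 0.245) | 52% | about 164 in total |
| Three-group F-test, largest difference 0.6 SD, two means equal (f = 0.6 × √2 / 3 = 0.283) | 65% | about 124 in total |
| 0.6 read as Cohen's f | over 99% | about 30 in total |

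No row gives 30 per group.

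**Step 5: what would give 80% at 30 per group.** The residual variance must fall to (0.6 / 0.736)² = 0.665 of the outcome variance.
- Baseline adjustment leaves 1 − r². Setting this to 0.665 gives r = √0.335, about 0.58. Power is 67% at r = 0.3, 75% at r = 0.5 and 81% at r = 0.6.
- Averaging the four follow-up assessments leaves (1 + 3ρ)/4. Setting this to 0.665 gives ρ of about 0.55, so 80% is reached if the mutual correlation is about 0.55 or less. This assumes equal variances, equal correlations and a 0.6 SD effect at every follow-up.

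**Step 6: dropout.** 90 / 0.75 = 120, against 122 stated. This step is close enough and is not the source of the gap.

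**The case against.** The strongest reply is that the article condenses a fuller document and names no test. Outcomes are measured at baseline and four times afterwards, so a baseline-adjusted or repeated-measures calculation is plausible. With a correlation near 0.58 it would give the printed 30 at the printed 80%. This stands in part. A reader might infer from step 1 that the trial must have 45 per group and that 30 is simply too few. The article does not support that, because it does not fix the analysis on which the figure depends. What remains is that the result does not follow from the inputs it is printed with.

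A reader might also infer that 80% is reachable only through baseline adjustment. That is too strong. Averaging the follow-ups can reach it, and a one-sided test against pooled controls gives about 85%. None of these routes is stated. The pooled one also sits badly with the Study interventions section, where the attention-control arm is there to separate out the effect of one-to-one contact.

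The article does not state sidedness, and its aims are partly worded as improvement. A one-sided reading is therefore possible, but alone it gives only 74%.

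Two further inferences lack support. Dividing the 5% between two contrasts would lower power again, to 51%, but no such split is stated. A null result need not be misread as excluding 0.6 SD, because the planned confidence intervals would show the imprecision.

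**Conclusion.** The concern holds in this form: the printed 80% power for an effect size of 0.6 with 30 completers per group cannot be reproduced from the printed inputs. Under a two-sided 5% pairwise comparison of a standardised mean difference, power is about 63%, 17 points below the claim. The difference detectable with 80% power is about 0.74 SD, and 80% power for 0.6 SD would take 45 per group.

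These figures rest on three assumptions: that 0.6 is a standardised mean difference, that the test is two-sided, and that the comparison is unadjusted. The first two are the ordinary reading of the text, and the third is all that the text describes. The finding is about the power statement. It does not show that 30 per group is indefensible under every analysis. Because this is the only basis given for the sample size on the primary outcome, the statement should be corrected or qualified.

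**What to change.** Rewrite the power statement in Sample size considerations in one of two ways.

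- **Restate the power.** Thirty completers per group give 63% power for a difference of 0.6 SD and 80% power for 0.74 SD, at a two-sided 5% level, for each pairwise comparison.
- **Make the power conditional.** Name a baseline-adjusted comparison as the primary analysis. State that 30 completers per group give about 80% power for 0.6 SD, two-sided 5%, if the baseline-outcome correlation is at least about 0.58, with 75% at a correlation of 0.5 and 81% at 0.6. This choice should be made before outcome data by group are examined.

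In either case, say that 0.6 is a standardised mean difference, if that is what was meant, and name the test and its sidedness. The change is one paragraph, plus a line in Statistical analysis under the second option. No extra recruitment is proposed. The cost is a less favourable power figure, or one that depends on a stated correlation.

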### Statistical analysis

Differences in primary and secondary outcomes between control and intervention groups will be compared using intention to treat analysis. Imputation methods will be used to assess data losses through level drop out and loss to follow up. All results will be reported as means and 95% confidence intervals.

### Time plan for the study

Participant recruitment began in April 2002 and by January 2006 all participants will have completed the trial and follow-up assessments of outcomes.
